**Methods/design:**

This is a prospective, randomized, controlled clinical trial that aimed to examine the capability of multimodal imaging techniques for the evaluation of CVR to improve treatment of patients with ischemic stroke. A total of 66 eligible patients will be recruited from Renji Hospital, Shanghai Jiaotong University School of Medicine. The patients will be categorized based on CVR into two subgroups as follows: CVR > 10% group and CVR < 10% group. The patients will be randomly assigned to medical management, percutaneous transluminal angioplasty and stenting, and intracranial and extra-cranial bypass groups in a 1:1:1 ratio. The primary endpoint is all adverse events and ipsilateral stroke recurrence at 6, 12, and 24 months after management. The secondary outcomes include the CVR, the National Institute of Health stroke scale and the Modified Rankin Scale at 6, 12, and 24 months.

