### Treatment protocol

The eligible patients underwent multimodal imagine to measure CVR. Regional CBF was quantitatively measured more than 3 weeks after the last ischemic attacks using computed tomography perfusion (CTP) or SPECT (123I-IMP). A study of a small number of patients with chronic arterial stenosis compared ASL perfusion with ACZ challenge with iodine 123 *N*-isopropyl-piodoamphetamine (123I-IMP) SPECT, and the fixed concentration of CO_2_ was provided by a gas-delivery system using a pressure transmitter to control the gas blender with prospective gas-targeting algorithms. Subjects underwent SPECT/CTP scanning, and were asked to breathe normally for 10 min. The region of interest (ROI) was designated manually in the cerebral cortex in the territory of the ipsilateral MCA at the level of the anterior horn of the lateral ventricle. ROIs were also placed in the bilateral cerebellar hemispheres and in the contralateral MCA territory as reference. Regional CBF was expressed as relative values (%) to normal control values of each institute obtained from volunteers free of cerebrovascular disease. CVR was calculated as follows:
$$ CVR\ \left(\%\right)=\left[\left({CO}_2\  challenge\  CBF- rest\  CBF\right)/ rest\  CBF\right]\times 100. $$

All treatment procedures and specific operating protocols for the management of ischemic stroke in our trial were standardized based on current guidelines.

Surgical intervention was microsurgical end-to-side anastomosis of a superficial temporal artery branch to a cortical branch of the MCA. If the superficial temporal branch was felt to be inappropriate, the occipital artery could be used. For participants in the surgical group, preoperative and postoperative antithrombotic treatments were carried out by a neurosurgeon. Patients in the PTAS group received stenting when “alarm” symptoms were relieved after MT. Participants in the nonsurgical group continued to receive the antithrombotic treatment preferred by their physicians. Targets for controlling risk factor were 130/85 mmHg for blood pressure, 100 mg/dL for low-density lipoprotein, 150 mg/dL for triglycerides, and 7% for hemoglobin A1C.

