### Study endpoints

Each patient was followed-up for 2 years by a neurologist and a neurosurgeon in each participating institute. Primary and secondary endpoints were defined as all adverse events and ipsilateral stroke recurrence at 6, 12, and 24 months after management, respectively. Neurological findings, intracranial CT/MRI, and CBF/CVR measurements were examined and reported at the time of enrollment and at 6 months, 1 year, and 2 years after enrollment. Evaluation of cognitive function and angiography were carried out at the time of enrollment and 2 years after enrollment. The functional outcomes were measured using CVR, the National Institute of Health stroke scale (NIHSS), and the Modified Rankin Scale (MRS) at 6, 12, and 24 months after the management.

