### Follow-up

In this trial, CTP and SPECT were followed-up 6 months after treatment. All the patients were followed-up after management by a neurosurgeon using a telephone interview or an in-person interview. The neurosurgeon was trained before the registry and was not involved in the treatment of ischemic-stroke patients. In outcomes after 6, 12, and 24 months, a MRS of 0–2 denoted a satisfactory outcome, and a score of 3–6 denoted a poor outcome.

Data verification was undertaken in 20% of all cases to assess the accuracy of data collection. The monthly audit, check of data quality, and statistical analysis were conducted by a third party who was in charge of notifying the principal investigator and Institutional Review Board of Renji Hospital about any issues that had arisen. Any serious adverse events were reported to the Institutional Review Board of Renji Hospital. Recommendations were forwarded to the principal investigators for reviewing risks and benefits. The Institutional Review Board had access to the interim results and made the final decision to terminate the trial.

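### Event endpoints are timed from an undefined date of management that differs by arm, and CVR and neurological status have conflicting time origins

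*Protocol article*

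**What the plan says.** **Event endpoints.** The abstract (Methods/design) sets the primary endpoint as "all adverse events and ipsilateral stroke recurrence at 6, 12, and 24 months after management". The Study endpoints section uses the same origin: "ipsilateral stroke recurrence at 6, 12, and 24 months after management". No version of the event endpoints timed from enrolment or randomisation appears anywhere. The Follow-up section likewise describes contact with patients as beginning after management.

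**What management is in each arm** (Treatment protocol):
- Nonsurgical: "Participants in the nonsurgical group continued to receive the antithrombotic treatment preferred by their physicians".
- PTAS: stenting was done when alarm "symptoms were relieved after MT". The abbreviation MT is not explained in the article.
- Bypass: the operation is described, with antithrombotic treatment before and after it. No waiting time is given.

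**CVR and neurological status.** In the Study endpoints section, neurological findings, CT/MRI and CBF/CVR "were examined and reported at the time of enrollment and at 6 months, 1 year, and 2 years after enrollment". The same section ends by timing CVR, NIHSS and MRS "at 6, 12, and 24 months after the management". The Follow-up section adds a third origin: "CTP and SPECT were followed-up 6 months after treatment".

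The Data collection section lists the timing of management among the recorded variables.

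**The concern.** A randomised comparison is protected from the moment of randomisation. A clock that starts at a later, arm-specific date gives up part of that protection. Here the stated origin has no clear start in the nonsurgical arm, where treatment simply continued. In the PTAS arm, stenting depends on how the patient does after an earlier step. If management is taken to be the procedure, a stroke before it precedes the clock, and a patient assigned to PTAS but never stented has no starting date. The procedural arms would then be judged on patients who reached their procedure, and the nonsurgical arm on everyone assigned to it. That would favour the procedural arms.

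The second problem is practical. CVR is the trial's central measurement, and one section gives it two origins. A site cannot tell which date sets the 6-month scan, and assessments made on different clocks cannot be lined up across arms.

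**Working it through.** **1. Passages side by side**

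| Outcome | Origin | Section |
|---|---|---|
| Adverse events, ipsilateral stroke recurrence | management | Abstract; Study endpoints |
| Neurological findings, CT/MRI, CBF/CVR | enrolment | Study endpoints |
| CVR, NIHSS, MRS | management | Study endpoints |
| CTP, SPECT | treatment | Follow-up |

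The direct contradiction falls on CVR, and on neurological status (neurological findings against NIHSS and MRS). The events have one stated origin; their problem is that this origin is undefined and depends on the arm.

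**2. The plan's own figure.** The Sample size section goes from 60 to 66 for about 10% loss: 60 × 1.10 = 66 (60/0.90 would give 67). The total does not depend on the time origin. With the abstract's three groups at 1:1:1, 66/3 = 22 per arm.

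**3. How many events could fall before a procedure?** The inputs are the medical-arm rates of stroke or death cited in the Introduction: 5.8% at 30 days and 15% at a median of 32.4 months. They come from another trial and serve only to show scale. The gaps are assumptions, because the article gives none.

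*Low scenario, constant hazard.* h = −ln(1 − 0.15)/32.4 = 0.00502 per month. Risk over a gap of d days = 1 − exp(−h × d/30.4).

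*High scenario, early risk concentrated in 30 days.* Up to day 30 the hazard is −ln(1 − 0.058)/30 = 0.00199 per day. After that it is [−ln(0.85) + ln(0.942)]/(32.4 − 30/30.4) = 0.00327 per month.

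Events = 22 × risk:

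| Assumed gap | Low risk | Low events per arm | High risk | High events per arm |
|---|---|---|---|---|
| 7 days | 0.12% | 0.03 | 1.38% | 0.30 |
| 14 days | 0.23% | 0.05 | 2.75% | 0.60 |
| 30 days | 0.49% | 0.11 | 5.80% | 1.28 |
| 90 days | 1.47% | 0.32 | 6.41% | 1.41 |

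**4. For comparison, expected events over 24 months**
- Low: 1 − exp(−0.00502 × 24) = 11.3%; 22 × 0.113 = 2.5.
- High: 1 − 0.942 × exp[−0.00327 × (24 − 30/30.4)] = 12.6%; 22 × 0.126 = 2.8.

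**5. Reading the result.** The table counts events left out; it does not give net bias. A 24-month window that starts at the procedure also ends later. Under a constant hazard the added follow-up largely makes up for the excluded period. The distortion matters mainly if early risk is concentrated, as in the high scenario. That scenario may itself be too high here, because the Treatment protocol has regional CBF measured more than 3 weeks after the last attack.

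**The case against.** Several stronger readings are tempting, and the article does not support them.

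- **That the switch from management to enrolment causes events to be lost.** It does not. The enrolment sentence covers imaging and neurological findings, and the events are timed from management throughout. Any loss would come from that choice of origin.
- **That events before the procedure are excluded.** No text says so. The 6-, 12- and 24-month points can be read as assessment times and not as the start of the risk window. In-hospital complications are recorded, and any serious adverse event goes to the review board. The loss is therefore conditional.
- **That bypass patients wait, or that unstented PTAS patients drop out of the endpoint.** No bypass wait is stated, and nothing is said about unstented patients. As MT is not expanded, PTAS-arm management might begin there and not at the stent.
- **That this is immortal-time bias.** Time before a clock that starts at the procedure is left out; it is not credited as event-free follow-up. The risk is of selection through delayed entry.
- **That procedural harm is hidden.** The 14.7% 30-day risk after stenting cited in the Introduction concerns the kind of early event that follows the procedure and would be counted.

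It can also be said that a condensed article leaves definitions to the full protocol or SAP. That answers a complaint about missing detail. It does not answer the two points that remain: the article itself states an origin after randomisation that differs by arm, and it contradicts itself on CVR and neurological status.

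**Conclusion.** The point holds in a limited form. Two things are established by the text. The event endpoints run from management, which is undefined by arm and cannot be the same date in each. CVR and neurological status carry conflicting origins that must be reconciled. The bias is conditional: if the clock starts at the procedure, earlier events in the procedural arms, and events in PTAS patients never stented, may go uncounted, to those arms' advantage.

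The size is uncertain. About 0.03 to 1.4 events per procedural arm of 22 could be left out, against about 2.5 to 2.8 expected over 24 months. This rests on assumed gaps of 7 to 90 days, on stroke-or-death rates borrowed from another trial's medical arm, and on 22 patients per arm. The effect may be negligible, but with so few expected events one omitted event would be noticeable. The change should be made, because it removes the question at little cost.

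**What to change.** Use the date of randomisation as the single time origin for all outcomes in all arms, and set the 6-, 12- and 24-month visits from it. Count every event from that date in the assigned arm, whether or not the procedure took place. Report the time from randomisation to procedure by arm, using the timing of management already collected. Correct the Abstract, Study endpoints and Follow-up sections so that they name the same origin. The condition for stenting is a clinical matter and is not touched.

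The cost is small. The sample size stays at 66. The change does assume that randomisation dates are on file, which is likely but not stated. Procedural-arm results may look slightly less favourable. The trial began on 6 June 2018 and this version was approved on 12 May 2019, so some visits may already have been made on another clock. Those should be analysed by their actual time from randomisation.

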### Data collection

The baseline data were collected including the following variables: hypertension, smoking status and whether diabetic, clinical presentation (i.e., initial ischemic stroke, on admission and before treatment); neurological functions (NIHSS and MRS), vascular stenosis, timing of management, treatment procedure, neurological conditions within 72 h after treatment, complications during hospitalization, follow-up, and presumed reasons of death. There is no storage of biological specimens for genetic or molecular analysis in the current trial and for future use in ancillary studies.

### Follow-up

In this trial, CTP and SPECT were followed-up 6 months after treatment. All the patients were followed-up after management by a neurosurgeon using a telephone interview or an in-person interview. The neurosurgeon was trained before the registry and was not involved in the treatment of ischemic-stroke patients. In outcomes after 6, 12, and 24 months, a MRS of 0–2 denoted a satisfactory outcome, and a score of 3–6 denoted a poor outcome.

Data verification was undertaken in 20% of all cases to assess the accuracy of data collection. The monthly audit, check of data quality, and statistical analysis were conducted by a third party who was in charge of notifying the principal investigator and Institutional Review Board of Renji Hospital about any issues that had arisen. Any serious adverse events were reported to the Institutional Review Board of Renji Hospital. Recommendations were forwarded to the principal investigators for reviewing risks and benefits. The Institutional Review Board had access to the interim results and made the final decision to terminate the trial.

### Sample size and data analysis

The number of patients included in the registry was equal to 60, and this trial involved 66 eligible ischemic-stroke patients, in which about 10% of patients were lost to follow-up. Data were presented as mean ± standard deviation (SD) for continuous variables, and as frequency for categorical variables. Significances between variables were analyzed using the chi-square test. Associations between clinical variables and outcomes were analyzed, and predictors of long-term outcome were identified using univariate and multivariate regression analyses. The difference was expressed as an odds ratio (OR, with 95% confidence interval (CI)), and *P* < 0.05 was considered statistically significant.

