The CVR is the ability of cerebral vessels to dilate or constrict in response to challenges or maneuvers [5, 6]. In addition, CVR is thought to be an important index of the brain’s vascular health, and provides vascular-reserve information that is complementary to steady-state vascular parameters, including CBF and CBV [7, 8]. There have been two main approaches to measuring CVR. One approach attempts direct CBF measurements of the brain tissue with flow-sensitive imaging techniques such as positron-emission tomography (PET), nuclear medicine (NM) techniques, computed tomography (CT) perfusion, or magnetic resonance imaging (MRI) perfusion before and after a vasodilatory stimulus. The second approach involves transcranial Doppler (TCD) measurement of flow velocities (typically in the middle cerebral artery (MCA)) distal to a lesion both before and after a vasodilatory stimulus, with the increase flow velocity considered a surrogate for CVR [9–12]. We intend to precisely evaluate the change of CVR before and after surgical or medical treatments by multimodal image including MRI, CT, and single-photon-emission computed tomography (SPECT), so that we can make strategies for individualized accurate diagnosis and treatment for the ischemic stroke [3, 13].

Due to the lack of effective therapeutic approaches for intracranial arterial stenosis or occlusion, the present trial was registered at the Chinese Clinical Trial Registry database, and approved by the Center for Reproductive Medicine at Renji Hospital (Shanghai, China). The present trial was designed to determine whether multimodal imaging data can effectively enhance the treatment strategy for adult patients with intracranial arterial stenosis or occlusion.

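### Chi-square and the odds ratio are assigned to variables in general, which does not fit CVR and NIHSS; followed as written, both would have to be cut at an unstated point, with a loss of power

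*Protocol article*

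**What the plan says.** All statistical methods are in the protocol article, section Sample size and data analysis. Four statements matter:

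- Continuous data are expected, but only described: "Data were presented as mean ± standard deviation (SD) for continuous variables".
- One comparison test is named, with no limit to categorical data: "Significances between variables were analyzed using the chi-square test".
- Regression is also named, for a specific purpose: "predictors of long-term outcome were identified using univariate and multivariate regression analyses".
- One effect measure is given: "The difference was expressed as an odds ratio", with a 95% confidence interval.

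The outcomes are listed elsewhere. The Abstract states: "The secondary outcomes include the CVR, the National Institute of Health stroke scale and the Modified Rankin Scale at 6, 12, and 24 months". Study endpoints calls the same three measures functional outcomes: "The functional outcomes were measured using CVR, the National Institute of Health stroke scale (NIHSS), and the Modified Rankin Scale (MRS". Treatment protocol defines CVR as the percentage change in blood flow from rest to CO2 challenge, which makes it continuous. The Introduction states an interest in change: "We intend to precisely evaluate the change of CVR before and after surgical or medical treatments by multimodal image".

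Only mRS has an outcome cut (0–2 against 3–6, in Follow-up). The 10% CVR threshold is used to group patients at entry and is not given as a definition of outcome. Baseline values are available: Study endpoints has CVR measured at enrolment, and Data collection lists NIHSS and mRS among the baseline data.

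**The concern.** A chi-square test and an odds ratio need categories. Two of the three secondary outcomes in the Abstract are numeric, and the article gives no cut for either as an outcome. An analyst who follows the text must choose a cut, and a cut chosen after the data are seen can influence the result. Any cut also discards information, which a trial of about 20 patients per arm can ill afford. CVR is the measure around which the trial is built, so a weak analysis of it touches the main scientific question even though it is not a primary endpoint.

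The interest in change from before to after treatment adds a second reason to be exact. Patients are grouped by the same baseline CVR from which change would be measured. In a group selected for low CVR, the mean tends to rise at the next measurement without any treatment effect (regression to the mean). The comparison that carries the conclusion should therefore be the one between randomised arms, and the article names no method for making it on numeric CVR.

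**Working it through.** **1. Sample size.** From Sample size and data analysis: base 60, loss about 10%, enrolled 66.
- 60 × 1.10 = 66, which reproduces the stated figure. (60 / 0.90 = 66.7 would round up to 67; the difference of one patient is immaterial here.)
- Allocation is 1:1:1, so 66 / 3 = 22 per arm enrolled and 60 / 3 = 20 per arm after loss.
- The base of 60 cannot be derived, because the article gives no effect size, SD, event rate or power.

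**2. Information kept by a cut.** For a normal outcome split at its median, the asymptotic efficiency relative to comparing means is 2/π = 0.637. In information, 60 patients act like 60 × 0.637 ≈ 38.

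**3. Power for two arms of 20.** Alpha is 0.05 in the article; two-sided is assumed. The standardised difference d and the baseline correlation r are assumptions, as the article states neither. The worked case is d = 0.8.

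- *Means:* power ≈ Φ(d√(n/2) − 1.96) = Φ(0.8 × √10 − 1.96) = Φ(0.570) = 72%. With the t distribution (38 df) it is 69%.
- *Chi-square after a cut midway between the two arm means* (a cut favourable to chi-square): the proportions above the cut are Φ(0.4) = 0.655 and Φ(−0.4) = 0.345, a difference of 0.311. The standard error is √(2 × 0.25 / 20) = 0.158 under the null and √(2 × 0.655 × 0.345 / 20) = 0.150 under the alternative. Power ≈ Φ((0.311 − 1.96 × 0.158) / 0.150) ≈ Φ(0.006) = 50%.
- *ANCOVA:* the residual SD shrinks by √(1 − r²). At r = 0.5, √0.75 = 0.866 and d becomes 0.8 / 0.866 = 0.924. Power ≈ Φ(0.924 × √10 − 1.96) = Φ(0.961) = 83%. With the t distribution (37 df) it is 81%.

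Other assumed values, by the normal approximation:

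| d | Means | Chi-square on cut outcome | ANCOVA, r = 0.3 | r = 0.5 | r = 0.7 |
|---|---|---|---|---|---|
| 0.5 | 35% | 23% | 38% | 45% | 60% |
| 0.8 | 72% | 50% | 76% | 83% | 94% |
| 1.0 | 89% | 69% | 91% | 95% | 99% |

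**4. Cross-check in patients.** For 80% power at d = 0.8, comparing means needs 25 per arm and chi-square on the cut outcome needs 40. The ratio 25 / 40 = 0.625 agrees with step 2.

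These figures apply to a roughly normal outcome such as CVR may be. NIHSS is an ordinal score; the direction of the loss is the same, but the percentages should not be carried over to it.

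**The case against.** **The article is a condensed account, and a fuller plan may name other tests.** Silence about the test for each secondary outcome would be no fault. Here, however, the text is not silent: it assigns a test and an effect measure to variables in general, in the same section that foresees continuous data. What stands of the objection is that the loss arises only if the analysis follows the article as written.

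**Regression is also named.** True, and a statement that the section offers nothing but chi-square and odds ratios would be wrong. But the regression is directed at predictors of long-term outcome, and the stated effect measure is an odds ratio. It supplies no comparison of numeric CVR or NIHSS between arms.

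**Chi-square is right for much of the trial.** This stands. Adverse events, ipsilateral stroke recurrence and dichotomised mRS are categorical, and the test suits them.

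Three stronger readings are tempting but not supported:

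- *That a rise in CVR in the low-CVR group would be credited to bypass or stenting.* The article speaks of evaluating and recording change but plans no within-arm test. Regression to the mean is shared by randomised arms in expectation, so it does not bias a comparison between them. It is a reason to specify that comparison; it does not show that the plan is biased.
- *That baseline CVR is left out as a covariate.* The article lists no covariates for its multivariate regression, so exclusion is not shown.
- *That a change in CVR may be a change of scanner.* Treatment protocol allows measurement "using computed tomography perfusion (CTP) or SPECT (123I-IMP"), and Follow-up mentions both at 6 months. Nothing says that a patient switches modality between visits.

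**Conclusion.** The point holds in a limited form. The named test and effect measure do not fit CVR and NIHSS, and following them forces a categorisation that the article does not define. For a normal outcome, a median split keeps about 64% of the information. With 20 per arm and d = 0.8, power is about 69–72% for means, about 50% for chi-square, and about 81–83% for ANCOVA at r = 0.5. The effect size, the correlation, normality, the position of the cut and the two-sided test are all assumptions; the size of the loss depends on them, but its direction does not. The primary endpoint, as the Abstract defines it, is unaffected. The matter should be corrected, but it does not invalidate the trial.

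**What to change.** Revise Sample size and data analysis before outcome data are examined:

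1. Restrict chi-square (or an exact test where counts are small) and odds ratios to the categorical outcomes: adverse events, ipsilateral stroke recurrence, and mRS 0–2 versus 3–6.
2. Compare follow-up CVR between randomised arms with a linear model, either ANCOVA at each visit or a mixed model over 6, 12 and 24 months, with baseline CVR as a continuous covariate. Report mean differences with 95% confidence intervals.
3. Compare NIHSS between arms with a rank-based or ordinal method adjusted for baseline NIHSS.
4. State that conclusions about change in CVR rest on the comparison between arms and not on change within a group, because patients are grouped by the same baseline CVR.

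The choice between ANCOVA and a mixed model, or between a rank-based and an ordinal method, can be left to the analysis plan. The cost is a few sentences. Baseline CVR and NIHSS are already collected, so no extra patients, visits or measurements are needed.

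### The only named test (chi-square) and the only named effect measure (odds ratio) do not fit cerebrovascular reactivity, a continuous outcome for which no outcome cut is given

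*Protocol article*

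**What the plan says.** All analysis statements stand in the protocol article under Sample size and data analysis.

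- Description: "Data were presented as mean ± standard deviation (SD) for continuous variables, and as frequency for categorical variables".
- Test: "Significances between variables were analyzed using the chi-square test". No other hypothesis test is named.
- Regression: "predictors of long-term outcome were identified using univariate and multivariate regression analyses". The type of regression is not given.
- Effect measure: "The difference was expressed as an odds ratio (OR, with 95% confidence interval (CI". No mean difference or other measure is named.

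The abstract lists the outcomes: "The secondary outcomes include the CVR, the National Institute of Health stroke scale and the Modified Rankin Scale at 6, 12, and 24 months". The Study endpoints section calls the same three functional outcomes and gives ipsilateral stroke recurrence as the secondary endpoint. The Treatment protocol section defines CVR as the percentage change in blood flow from rest to CO2 challenge, which is a continuous quantity. The only outcome cut in the article is in the Follow-up section: modified Rankin 0–2 against 3–6. The 10% CVR threshold (abstract and Study design) sorts patients at entry.

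**The concern.** The article does not leave the analysis open. It names one test and one effect measure in general terms, and neither can take CVR as it is measured. To apply them, an analyst must first cut follow-up CVR into categories. With no cut stated, the cut could be chosen after the data are seen.

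This matters because CVR is the variable that the trial is built around. The Introduction sets out to evaluate its change from before to after treatment, and Study endpoints schedules it at enrollment and at follow-up. A chi-square table uses neither the size of a change nor the baseline value. With about 20 evaluable patients per arm, there is little information to spare.

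**Working it through.** **Inputs from the article.** 60 patients, 66 with allowance for about 10% loss, and allocation 1:1:1. I take the three arms named in the abstract. P < 0.05 is read as two-sided.

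**The article's own figure.** 60 × 1.10 = 66, and 60 / 0.90 = 66.7, or 67. The 66 is reproduced to within one patient. Evaluable patients per arm: 60 / 3 = 20. The 60 itself cannot be derived, because no effect size, SD, event rate or power is stated.

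**Assumed inputs.** Normal follow-up CVR, one arm shifted by d = 0.8 SD, a cut at the centre of the distribution, and baseline/follow-up correlation r of 0.3, 0.5 or 0.7. The article gives none of these.

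**Two arms, 20 per arm.**

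1. Comparison of means: power = Φ(d / √(2/n) − 1.96) = Φ(0.8 / 0.316 − 1.96) = Φ(0.57) = 72%.
2. Central cut, then chi-square: the proportions above the cut are 1 − Φ(0.4) = 0.345 and Φ(0.4) = 0.655. Power = Φ((0.311 × √20 − 1.96 × √(2 × 0.5 × 0.5)) / √(2 × 0.345 × 0.655)) = Φ((1.390 − 1.386) / 0.672) = Φ(0.006) = 50%.
3. Baseline-adjusted comparison: the residual SD shrinks to √(1 − r²), so the effective d is 0.8 / √(1 − r²).
   - r = 0.3: d = 0.839, power 75%
   - r = 0.5: d = 0.924, power 83%
   - r = 0.7: d = 1.120, power 94%

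**Three arms of 20, one arm shifted by 0.8 SD (simulation).**

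| Analysis of CVR | Power |
|---|---|
| 3 × 2 chi-square, central cut | 47–53%, depending on run and on how the centre is set |
| 3 × 2 chi-square, cut at the pooled 80th percentile | 43% |
| 3 × 3 chi-square, cut at tertiles | 50% |
| ANOVA on the continuous value | 72% |
| ANCOVA, r = 0.3 / 0.5 / 0.7 | 75% / 83% / 95% |

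With no true difference, ANOVA, ANCOVA and the central-cut chi-square reject in about 5% of trials, so the gaps are not bought with false positives. A third category recovers nothing, and an uneven cut costs more.

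**Sensitivity to the shift (two arms, pooled-median cut).**

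| d | Means | Chi-square |
|---|---|---|
| 0.5 | 35% | 23% |
| 0.8 | 72% | 50% |
| 1.0 | 88% | 69% |
| 1.2 | 97% | 84% |

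The loss is 12 to 22 points over this range. At d = 0.886, where 20 per arm give 80% power for means, the chi-square test would need 33 per arm.

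**The case against.** The strongest reply is that the article nowhere says CVR or NIHSS will be dichotomised. A reader might infer that following the plan means cutting both, but the text does not support that. No outcome cut is given for either, the chi-square sentence does not mention CVR or NIHSS, and regressions of unstated type are also planned. This stands, and the loss above is therefore conditional.

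The reply also stands for NIHSS. A proportional-odds model gives an odds ratio on the uncut score, so regression plus odds ratio can suit NIHSS as written. Nor can the mean ± SD sentence be held against NIHSS, because the article does not class it as continuous.

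A reader might also say that two of the three secondary outcomes are affected. That count follows the abstract only. Under Study endpoints, the primary and secondary endpoints are adverse events and stroke recurrence, for which chi-square and the odds ratio are suitable. CVR remains a listed outcome in both places.

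Finally, methods for individual secondary outcomes are often left to an analysis plan, which is not shown here. That would answer an omission. It does not answer a general statement that gives one test and one effect measure with no limit on scope. Ordinary linear regression, the natural model for CVR, yields no odds ratio, so the regression sentence does not rescue CVR as it would NIHSS.

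**Conclusion.** The point holds for CVR: the article names no test or effect measure that can use it as measured, or use its baseline value. It does not hold as a claim that the plan dichotomises CVR and NIHSS. For NIHSS, only the type of regression needs stating.

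If the named test were applied to CVR, power would be about 50%, against 72% for ANOVA. That is the like-for-like gap. The further gain to 75–95% comes from baseline adjustment, a separate choice. These figures rest on 20 per arm, an assumed 0.8 SD shift, normality, a central cut and assumed correlations. They illustrate the cost and are not an estimate of this trial's power. The point should be corrected, but it leaves the analysis of the event endpoints untouched.

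**What to change.** In Sample size and data analysis:

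- Restrict chi-square and binary odds ratios to binary outcomes: adverse events, ipsilateral stroke recurrence, and modified Rankin 0–2 against 3–6.
- For CVR, compare arms by ANCOVA with baseline CVR as covariate at each visit where CVR is measured. Report the between-arm mean difference with its 95% CI.
- For NIHSS, state that the regression is ordinal (proportional odds, adjusted for baseline NIHSS). This keeps the odds ratio and needs no cut. If the regressions were already meant this way, say so.

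Reconcile which visits include CVR imaging: Study endpoints gives 6 months, 1 year and 2 years, while Follow-up mentions CTP and SPECT at 6 months only. ANCOVA by visit works under either schedule.

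The cost is wording. Baseline CVR is scheduled at enrollment (Study endpoints) and baseline NIHSS is in the collected data (Data collection), so no new measurement is needed.
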